## Abstract

**Background:**

Incisional hernia is the most frequently seen long term complication after laparotomy causing much morbidity and even mortality. The overall incidence remains 11-20%, despite studies attempting to optimize closing techniques. Two patient groups, patients with abdominal aortic aneurysm and obese patients, have a risk for incisional hernia after laparotomy of more than 30%. These patients might benefit from mesh augmented midline closure as a means to reduce incisional hernia incidence.

**Methods/design:**

The **PRI**mary **M**esh Closure of **A**bdominal Midline Wound (PRIMA) trial is a double-blinded international multicenter randomized controlled trial comparing running slowly absorbable suture closure with the same closure augmented with a sublay or onlay mesh. Primary endpoint will be incisional hernia incidence 2 years postoperatively. Secondary outcomes will be postoperative complications, pain, quality of life and cost effectiveness.

A total of 460 patients will be included in three arms of the study and randomized between running suture closure, onlay mesh closure or sublay mesh closure. Follow-up will be at 1, 3, 12 and 24 months with ultrasound imaging performed at 6 and 24 months to objectify the presence of incisional hernia. Patients, investigators and radiologists will be blinded throughout the whole follow up.

**Disccusion:**

The use of prosthetic mesh has proven effective and safe in incisional hernia surgery however its use in a prophylactic manner has yet to be properly investigated. The PRIMA trial will provide level 1b evidence whether mesh augmented midline abdominal closure reduces incisional hernia incidence in high risk groups.

**Trial registration:**

Clinical trial.gov NCT00761475.

## Background

Incisional hernia (IH) is the most frequently seen long term complication in surgery causing much morbidity and even mortality in patients [1-4]. Despite studies on the optimal closing technique for laparotomies, the risk for IH after midline incision remains about 11-20% [5,6]. In the Netherlands alone about 4000 IH operations are performed each year. Incisional hernia surgery is, in fact, a re-operation to relieve symptoms caused by this common complication and the results of repair are often disappointing [7,8].

Patient-related risk factors for incisional hernia after a laparotomy, like obesity, steroid use, malnutrition, smoking, abdominal aortic aneurysm (AAA), and connective tissue disorders are known [7,9-13]. Despite this knowledge a sufficient method for prevention, has not been developed yet. Most research in the field of incisional hernia surgery has been performed to prevent recurrence after repair. The closure technique of midline incisions has grosso modo remained unchanged since many decades and primarily consists of suturing the linea alba. Interest in prevention of incisional hernias with the aid of synthetic mesh is growing and small, yet promising studies have now been published [14-25].

One specific group of high-risk patients are patients with an AAA. Aortic aneurysm is considered to be related to a type of connective tissue disorder. The connective tissue in these patients is thought to be compromised, playing an important role in the pathogenesis of an aneurysmal distension of the aorta. Healing of the midline fascia after laparotomy may be compromised due to formation of collagen with insufficient strength. Sutures can tear through the fascia and defects can develop in the abdominal wall. The relationship between aortic aneurysm and other abdominal wall hernias, like inguinal hernias, has been reported [26-28]. Retrospective and prospective studies have shown an average risk for incisional hernia after AAA repair of about 30% (Table 1) [9,26,28-34].

**Table 1 T1:** Publications concerning risk for incisional hernia after aortic aneurysm repair with midline incision with a minimum of 2 years follow-up

**Author**	**Year**	**Follow-up**	**Article type**	**# Hernias**	**# AAA**	**%**
Fassiadis et al. [9]	2005	50 months	RCT	20	22	90,9
Rodriguez et al. [29]	2004	36 months	Prospective	14	61	22,9
Liapis et al. [30]	2004	63 months	Prospective	32	197	16,2
Raffetto et al. [28]	2003	33 months	Prospective	50	177	28,2
Augestad et al. [31]	2002	42 months	Case series	49	140	35
Musella et al. [32]	2001	49 months	Prospective	16	51	31,4
Adye and Luna [26]	1998	36 months	Retrospective	18	58	31,0
Holland et al. [33]	1996	24 months	Case series	13	34	38,2
Stevick et al. [34]	1988	38 months	Retrospective	10	27	37,0

Another high risk group is the group of obese patients [5]. Patients with a BMI of 30 or more have a high risk of developing an incisional hernia after midline incision, with an incidence of 22% after 12 months [5,13]. Most recent literature is showing us that even a BMI of more than 27 gives a 20% risk for developing an incisional hernia after midline laparotomy [35]. Considering only 50% of incisional hernia will be clinically evident in the first 12 months, the total incidence is likely to be above 30%. It is known from the study of Burger et al. that an extensive follow up time of up to 10 years is needed to evaluate outcome in hernia surgery [7]. A tailored approach might be necessary, since hernia formation is multifactorial. Thus, the above mentioned high-risk group of patients with obesity and aneurysmal disease can benefit most from prevention.

Some small studies have been performed to evaluate the effect and safety of primary laparotomy wound closure with the aid of prosthetic mesh (Table 2) [14-25]. These studies show a very low risk for incisional hernia and a low infection rate, even when used in contaminated area’s, as seen in colostomy surgery. However, no high quality and adequately powered randomized controlled trial has been performed to evaluate the impact of prophylactic mesh augmentation for prevention of incisional hernia in high risk patients. This is the reason that the **PRI**mary **M**esh Closure of **A**bdominal Midline Wound (PRIMA) trial is being conducted.

**Table 2 T2:** Publications concerning incisional hernia prevention with the aid of prosthetic mesh

**Author**	**Year**	**Type article**	**# Patients**	**Hernia primary**	**Hernia Mesh**	**Follow-up**	**Mesh type**	**Mesh position**
G. Currò et al. [14]	2011	Prospective	95	15/50	2/45	24 months	Polypropylene	Sublay
O. H. Llaguna et al. [15]	2011	Prospective	134	11/62	1/44	17 months	Biological	Intraperitoneal
P. M. Bevis et al. [16]	2010	RCT	85	16/43	5/37	36 months	Polypropylene	Sublay
G. Currò et al.	2010	Prospective	50	8/25	1/25	12 months	Polypropylene	Sublay
M. P. Hidalgo et al.	2010	Cohort	72	-	0/72	46 months	Polypropylene	Onlay
O. H. El-Khadrawy et al. [19]	2009	RCT	40	1/20	3/20	36 months	Polypropylene	Preperitonial
G. Hebert et al.	2009	Cohort	16	-	1/16	6 months	Mix	Sublay
J. Strzelczyk et al. [21]	2006	RCT	74	8/38	0/36	28 months	Polypropylene	Sublay
J.L. O’Hare et al. [22]	2007	Cohort	39	-	1/28	48 months	Polypropylene	Sublay
C. Gutierrez de la Pena et al. [23]	2003	RCT	88	5/44	0/44	36 months	Polypropylene	Onlay
J. Strzelczyk et al. [24]	2002	Prospective	60	9/48	0/12	12 months	Polypropylene	Sublay
A. Pans [25]	1998	RCT	288	41/144	33/144	29 months	Vicryl	Intraperitoneal

### Objective

The objective of this study is to evaluate the effectiveness of incisional hernia prevention in patients after laparotomy for aortic aneurysm and in obese patients with a BMI of more than 27. A double blind randomized controlled trial will compare the commonly used technique of running suture to closure with the aid of a prosthetic mesh.

•The primary outcome measure will be incisional hernia occurrence 2 years postoperatively.

•Secondary outcome measures will cover relevant postoperative complications, post-operative pain and quality of life.

## Methods/design

### Trial design

The trial is a double blinded randomized controlled international multi centre trial comparing traditional closure with running slowly absorbable suture to closure with the aid of prosthetic mesh. A total of 11 centers have agreed to participate in the trial which are located in three different countries (The Netherlands, Germany and Austria). A total number of 460 patients will be included. Patients will be randomized in three groups per-operatively to either receive primary closure, or mesh supported closure either in a sublay or onlay position. Patients will be kept unaware of the procedure until the endpoint of the trial was assessed. Outpatient clinic controls will be done by surgeons or surgical residents blinded for the procedure. Results will be stratificated by center and operation indication.

### Participants

Patients meeting the inclusion criteria scheduled for elective laparotomy will be asked to participate in the study. After ample information has been given, patients will be asked for informed consent.

### Inclusion criteria

•Every elective midline laparotomy for patients with Abdominal Aortic Aneurysm AND/OR patients with a BMI of more than 27^a^.

•Signed informed consent

### Exclusion criteria

•Age < 18 years

•Inclusion in other trials with interference of the primary endpoint

•Life expectancy less than 24 months (as estimated by the treating physician)

•Pregnant women

•Immune suppression therapy within 2 weeks before surgery

•Bovine allergy

### Registration and randomization procedure

Patients who are scheduled for operation and who have given informed consent will be registered by contacting the trial coordinator using the telephone or using the online inclusion randomization system. Included patient are registrated in an online data base (designed and managed by HOVON data center, Rotterdam, the Netherlands) called TOP (Trial Online Process; see http://www.primatrial.nl). The patient name code, date of birth, name of caller, name of responsible physician, sex and eligible criteria will be registered. Every participating institution has its own login code.

Randomisation will take place at the end of the scheduled operation before closing the abdomen in the operating room by contacting the trial coordinator using the telephone or using the online inclusion randomization system. The patient will stay in the randomization group on an intention to treat principle.

### Intervention

Patients will be randomized for three different closing techniques (1A: primary suture closure of the midline fascia, 2B onlay mesh supported closure and 3C sublay mesh supported closure). Both mesh techniques are extensively used in incisional hernia surgery. However, a powered randomized comparison of these two techniques has not been performed. Infection rates in these trials seem low, even in the presence of open bowel [36-41]. Because the study population will not be operated for an incisional hernia, which necessitates extended dissection of the abdominal wall in a previously operated area, infection rates are expected to be lower than the rates mentioned in the literature. Intra-peritoneal placement has not been considered given the high risk for adhesions between viscera and mesh [42].

The mesh will be fixed to the fascia structures with fibrin sealant (Tissucol DUO 500 2,0 ml (Baxter Deutschland GmbH, Unterschließheim, Germany) in order to avoid sutures subcutaneously, to prevent the production of seroma and to simplify the procedure [43]. Nowadays fibrin sealants are occasionally used in inguinal hernia surgery [44-46]. The mesh will be fixed adequately with fibrin sealant to the ventral part of linea alba and posterior rectus sheath. The Optilene Mesh LP, 6 × 35 cm, B. Braun Aesculap AG, Tuttlingen, Germany, will be used as it was shown to have an optimal fixation with fibrin sealant and to provide good tensile strength [47].

Only the first operations of each center will be supervised by one of the PRIMA trial research fellows. If during operation an incisional hernia was discovered the patient was excluded from the trial, as the interest of this study was incisional hernia prevention, not repair. All centers were familiar with the 4:1 suture length to wound length ratio concept although not measured. As the focus of the trial was on the effect of primary mesh augmentation versus common day practice closure, no measurements of the suture closure were done.

#### Group A. Primary closure of the midline

The midline fascia will be closed in all three groups with a running slowly absorbable suture *(MonoPlus, USP 1, Needle HRT48, 150 cm loop, B.Braun Aesculap, Tuttlingen, Germany).* The ratio of suture length to wound length of 4:1 is recommended (but not measured). Subcutaneous tissue and skin are closed in a fashion preferred by the surgeon.

### Mesh supported closure

#### Group B. Onlay mesh supported closure

First, the midline will be closed as indicated in group A.

The Optilene Mesh LP will be positioned on the primary closed midline fascia with an overlap of 3 cm at each side. The mesh will then be fixed with fibrin sealant (5 ml). The fibrin sealent will be applied on the entire surface of the mesh, and in one shot having permanent contact between the mesh and the tip of the joining piece. Immediately after application of the fibrin sealant, the mesh will be smoothed with the back of a forceps to get a good fixation of the mesh on the entire surface and especially on the suture line. If present, it is also possible to use spray fixation using the EASYSPRAY system, *Deutschland GmbH, Unterschließheim, Germany.* When laparotomy is larger then 25 cm use 2 applicators of Tissucol (10 ml). Subcutaneous tissue and skin are closed in a fashion preferred by the surgeon.

#### Group C. Sublay mesh supported closure

A space will be created between both posterior rectus sheaths and the rectus muscle. Both posterior rectus sheath edges are sutured using a running slowly absorbable suture,*(Monoplus, USP1, Needle HRT48, 150 cm, B. Braun Aesculap AG, Tuttlingen, Germany)*. A suture length to wound length ratio of 4:1 was recommended (not measured). The Optilene Mesh LP will then be placed between the posterior rectus sheath and the rectus muscle with an overlap of 3 cm at each side and fixed with fibrin sealant (5 ml). The fibrin sealent will be applied on the entire surface of the mesh, in one shot having permanent contact between the mesh and the tip of the joining piece. Immediately after application of the fibrin sealant, the mesh will be smoothed with the back of a forceps to get a good fixation of the mesh on the entire surface and especially on the suture line. If present, it is also possible to use spray fixation using the EASYSPRAY system, *Deutschland GmbH, Unterschließheim, Germany.* When laparotomy is >25 cm use 2 applicators of Tissucol (10 ml). The midline anterior rectus sheath will be closed using a running slowly absorbable suture *(Monoplus, USP1, Needle HRT48, 150 cm, B. Braun Aesculap AG, Tuttlingen, Germany)*, covering the mesh. A suture length to wound length ratio of 4:1 was recommended (not measured). Subcutaneous tissue and skin will be closed in a fashion preferred by the surgeon.

#### Postoperative treatment

Wound drainage will not be routinely applied. Seromas do not have to be punctured or drained, but can be left untreated to resolve spontaneously.

### Implementation

#### Pre-operative data

•Date of birth

•Length and weight

•Smoking history (current smoker ( Y or N )

•Medical history (COPD, diabetes, cardiac disease)

•Preoperative Radiotherapy or chemotherapy

•Preoperative corticosteroids

•Postoperative corticosteroids

•Previous abdominal operations

•Other abdominal hernias (inguinal, umbilical, epigastric hernias)

•ASA class

•Width of linea alba (when pre-operative C.T. imaging is available)

•Size of aneurysm and location

•Epidural catheter

#### Operation data

•Type of operation

•Type and length of prosthesis

•Volume of fibrin sealant applied

•Length of incision

•Blood loss

•Operation time

•Antibiotic prophylaxis

•Suture material

•Drains and location

•Thrombosis prophylaxis

•Pain medication

•Complications (intestinal lesions, bleeding, other)

#### Post-operative data

•Blood transfusion

•Postoperative ventilation and duration

•Postoperative ileus and duration

•Postoperative complications:

○ Surgical Site Infection, according to the guidelines proposed by Mangram in 1999 [48]. (Appendix)

○ Wound hematoma: accumulation of blood in the wound area, which warrants surgical exploration and intervention.

○ Seroma subcutaneously

○ Pulmonary infections

○ Ventilation problems

○ Re-intervention and difficulties caused by the mesh at re-entry

○ Re-admission and indication

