#### Outpatient follow-up

The follow-up schedule is displayed in Table 3. During visits the following information will be gathered.

•Outpatient clinic visit at 1, 3, 12 and 24 months

○ Incisional hernia

○ Wound infection

○ Seroma formation

○ Other wound problems

○ Inguinal hernia

•Ultrasound at 6 and 24 months

•VAS score at 1 month

•VAS scores and Quality of Life forms preoperatively ( day of operation or the day before) and at 3, 12 and 24 months

**Table 3 T3:** Follow up schedule

**Evaluation moments**	**MOS SF-36 (1)**	**EQ-5D (2)**	**VAS score (3)**	**Outpatient clinic**	**Ultrasound**
Pre-operative	X	X		X	
1 month			X	X	
3 months	X	X	X	X	X at 6 months
12 months	X	X	X	X	
24 months	X	X	X	X	X

(1) MOS SF-36: Questionnaire concerning quality of life (SF-36 ™ Health Survey, Medical outcomes Trust, Boston, Massachusetts 02116, USA).

(2) EQ-5D: Euro Qol Group quality of life questionnaire.

(3) VAS score: Pain measurement tool on which patients can define their pain on a sliding scale.

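### The post-operative complication list counts only subcutaneous seroma, a limit that follows the mesh plane under randomisation and that the clinic-visit list does not share

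*Protocol article*

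**What the plan says.** Under Post-operative data, the complications to be collected include "Seroma subcutaneously". No criteria, threshold or time window accompany it.

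Under Outpatient follow-up, the seroma item is "Seroma formation", with no location. It is collected at this schedule: "Outpatient clinic visit at 1, 3, 12 and 24 months". The same visits also have a catch-all item, "Other wound problems".

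The two mesh arms differ by tissue plane. For onlay, the mesh is "positioned on the primary closed midline fascia with an overlap of 3 cm at each side", and subcutaneous tissue is then closed over it. For sublay, the mesh is "placed between the posterior rectus sheath and the rectus muscle", and the anterior rectus sheath is then closed over it.

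The Abstract and the Objective section name postoperative complications first among the secondary outcomes. The Intervention section gives seroma prevention as one reason for fixing the mesh with fibrin sealant. The Postoperative treatment section speaks of seromas without a location and allows that they may settle without intervention.

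**The concern.** An outcome compared between randomised arms should have the same chance of being recorded in each arm. Here the limiting word in the post-operative item picks out one tissue plane, and the plane in which the mesh lies is what distinguishes onlay from sublay. A collection at the mesh qualifies by its location in one arm and fails by its location in the other, whatever its size or clinical consequence.

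At stake is the credibility of the seroma figures by arm. The Intervention section says that no powered randomised comparison of the two mesh techniques exists. The Statistical analysis section aims at non-inferiority of onlay to sublay on hernia. If that is shown, wound complications are a natural basis for choosing between the techniques, and even a descriptive seroma table would be read for that purpose. That use is an inference; the article does not state it.

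**Working it through.** No arithmetic in the article bears on this point: it gives no seroma rate, no split by plane and no power statement for seroma. The check is to set the texts side by side.

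**1. Does the mesh plane decide whether fluid at the mesh qualifies?**

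| Collection | Post-operative data item | Outpatient follow-up item |
|---|---|---|
| At an onlay mesh (on the closed fascia) | meets the wording | meets the wording |
| At a sublay mesh (behind the rectus muscle, under the closed anterior sheath) | does not meet the wording | meets the wording |
| In the subcutaneous layer, any arm | meets the wording | meets the wording |

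The two lists disagree only in the sublay-mesh row. Under-recording is therefore partial, since a subcutaneous seroma in a sublay patient still counts. Where it occurs, it lowers the sublay count. Suture-only closure creates no retromuscular space, so the same asymmetry applies to sublay versus suture closure.

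**2. Is the restriction part of a general pattern?** No. In the same list, hematoma is located in the wound area generally. The infection item refers to criteria in the Appendix that extend to fascia and muscle. Seroma is the only complication in that list limited to a layer.

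**3. Does the visit item close the gap?** In part. From the 1-month visit on, a detected collection in any plane has a place on the form. The first visit is at 1 month, and the article itself expects that seromas may resolve unaided. It does not say whether the 1-month entry covers everything since surgery or only what is present that day. If only the latter, a collection that came and went earlier can be entered as a seroma only under the post-operative item, where the restriction applies.

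**4. Which item feeds the outcome?** The article does not say. Two seroma items of different scope exist, and neither is named as the source for the complication comparison.

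**5. How large could the effect be?** Let p be a true seroma rate common to both mesh arms, and f the share of sublay seromas that are purely retromuscular and so unrecorded. The recorded rates are then p for onlay and p(1 − f) for sublay, a spurious difference of p × f. The article gives neither p nor f, so the expression shows direction but not size.

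**The case against.** The strongest case against is that the visit list already records seroma in every plane, in all arms, at four visits, with a catch-all wound item beside it. The Post-operative data section is a collection list rather than a set of endpoint definitions, and it nowhere says that other collections are excluded. It also collects re-interventions and re-admissions, so a deep collection with serious consequences would leave a trace. The only onlay versus sublay comparison in the Statistical analysis section is on hernia. Finally, a journal article commonly leaves detailed complication definitions to the full protocol.

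Much of this stands. A reader might infer that fluid around a sublay mesh is never counted and that the safety comparison is therefore biased towards sublay. The document does not support that: the visit item counts such fluid, and no analysis is tied to the post-operative item alone.

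A reader might also attach a size. Assume a 15% true rate in both mesh arms, the planned 180 patients each, and 25%, 50% or 75% of sublay seromas missed. The recorded rates are then 15% against 11.3%, 7.5% or 3.8%. With standard errors of 0.0355, 0.0331 and 0.0301, z is 1.06, 2.27 and 3.73. The arithmetic is right, but the 15% and all three shares are assumptions with no source in the article. The calculation also supposes that the visit item recovers none of the missed events, which its wording contradicts. It cannot serve as an estimate for this trial.

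Two parts of the objection do not carry. Leaving detail to the full protocol would excuse a missing definition, but this restriction is stated, and a second section does not repeat it. The absence of a planned seroma test does not make unequal recording harmless, because complications are a declared outcome of a randomised trial and will be reported by arm.

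**Conclusion.** The point holds in a limited form. The article contains two seroma items of different scope, and the narrower one depends on the plane that distinguishes the mesh arms. A seroma comparison that uses the post-operative item can under-record sublay seromas, chiefly those that resolve before the 1-month visit. The direction follows from the texts; the size cannot be derived from them.

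The conclusion rests on two assumptions: that those completing the form take the limiting word literally, and that the post-operative item contributes to the complication outcome. If the sponsor confirms that the analysed outcome is the unrestricted item, and that it also covers the first month, only a wording mismatch remains. The primary hernia endpoint is unaffected. This is a cheap improvement, not a flaw in the design.

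**What to change.** Delete the word that limits seroma to the subcutaneous layer in Post-operative data. Use one wound seroma item, in any plane, with identical wording there and in Outpatient follow-up, applied alike in all three arms. State that this item is the seroma outcome compared between arms.

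Two additions should be avoided. A seroma search should not be attached to the ultrasound: the article describes that examination for hernia detection, and at 6 and 24 months it would probably miss early collections that have resolved. Outpatient assessors and radiologists should not be asked to record whether fluid lies around a mesh or in which plane, because they are to remain blinded and that question points to the allocation.

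The cost is a change of wording on the form. Some deep collections of little clinical consequence will be counted, and recorded sublay rates may rise. The change removes unequal eligibility by wording; it does not make deep collections as easy to find on examination as superficial ones.
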